### Statistical analysis

Consistent with National Institutes of Health recommendations for pilot and feasibility studies, this trial is not designed for statistical power to definitively test effectiveness hypotheses [48]. Quantitative data related to implementation will be presented descriptively. Linear and logistic regression modelling will be used, as appropriate, to compare effectiveness outcomes between the control and intervention groups in order to test the feasibility of our assessment and analytic strategies (Table 2). Complete case analysis will be used as a primary approach to missing data. If there is a large amount of missing data, multiple imputations will be used to mitigate the effects of missing data.

Semi-structured interviews related to IntACT’s implementation will be recorded, transcribed and de-identified. Subsequently, the transcripts will summarized and deductively analyzed according to the domains of the PRISM implementation framework using a Rapid Qualitative Analytic approach [49–51]. Qualitative themes pertaining to intervention implementation will be identified from the summaries and compared with quantitative data to identify cross-cutting themes related to intervention acceptability, appropriateness, and feasibility. Mixed methods research frameworks (e.g., joint display) will be used to draw inferences from the combined quantitative and qualitative implementation data [52,53].

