### Study design

The IntACT pilot study is a single-site RCT that will enroll patients with SUD during an index hospitalization and randomize them to receive IntACT or Usual Care over an intervention period of 4 months (Fig 1) [35]. Randomization is unbalanced, with a ratio of 3:2 favoring the intervention arm over Usual Care. This randomization scheme is intended to prioritize data collection about the feasibility and implementation of IntACT by favoring assignment to the intervention arm. Additionally, we expect IntACT to be superior to Usual Care and therefore have an ethical rationale for more participants receiving the intervention. Finally, unbalanced randomization has only slightly less power than a balanced design when the absolute differences between the groups are small [36,37]. The randomization sequence will be developed by an impartial third party at the University of Utah Clinical and Translational Science Institute using random permuted blocks and embedded into a secure online platform (REDCap). The allocation sequence will be concealed until the time of assignment to IntACT or Usual Care. While the nature of the intervention precludes masking for patients and clinicians, statisticians will be masked to study arm assignment.

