### Recruitment and eligibility

Recruitment will occur at a single 425-bed tertiary academic medical center. A total of 75 patients will be recruited. Patient inclusion criteria include: 1) aged 18 years and older, 2) hospitalized at the study site for any medical reason, and 3) Electronic Health Record (EHR) documented diagnosis of any SUD. Exclusion criteria are: 1) currently incarcerated, and 2) Tobacco Use as the only documented SUD. Potential participants will be identified through a combination of clinician referral (i.e., the study will be advertised to hospital clinicians and staff, and hospital care teams and the addiction consult service can refer patients to the study) and prescreening. The prescreening process will consist of the IntACT research coordinator reviewing a curated list of daily hospital admissions filtered to contain new medical admissions with a documented SUD. Admission can be for any medical cause. Patients from the prescreening list that appear to meet eligibility criteria after EHR review will be approached and screened for enrollment.

Additionally, 20 clinicians who interact with IntACT will be recruited from both inpatient and outpatient settings to assess IntACT’s feasibility and acceptability. Clinician inclusion criteria include: 1) aged 18 years and older, 2) provided direct clinical care in any capacity to enrolled patients either in the hospital or in the outpatient setting (e.g., hospitalist, PCP, specialist/consultant), and 3) interact with the IntACT team in a clinical/shared patient care capacity (e.g., coordinated discharge planning). Exclusion criteria include an inability to complete surveys and/or interviews in English or Spanish. Potential participants will be identified through review of clinical EHR notes for enrolled patients and through word of mouth from the IntACT clinical team.

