For the clinician cohort, potentially eligible clinicians (i.e., those identified as providing clinical care to intervention patients) will be contacted by study staff either verbally or via secure institutional email and screened for eligibility based on inclusion/exclusion criteria. If eligible, research staff will assess interest in participation and conduct a formal informed consent process for those who wish to enroll. To minimize any possibility of undue influence, clinician recruitment will be conducted by the research coordinator or study staff, not by supervising physicians or direct clinical colleagues.

In addition to recruitment and enrollment, study procedures also involve iterative assessment of primary and secondary study outcomes (Table 1). Outcome assessment will be led by study staff and take place at scheduled in-person study visits or, if necessary, remotely over telephone or videoconferencing. These assessments will consist of a series of surveys and occur at baseline, 2, 4, and 6 months after randomization. Patient participants will be compensated $35 for completing each of the first three assessments (i.e., baseline, 2 month, 4 month) and $75 for completing the final 6-month close-out visit (total potential earnings $180). Purposive sampling will be used to recruit fifteen intervention participants who completed the final close-out visit to participate in a 45-minute semi-structured interview about their experience with IntACT. Compensation for completing the interview will be $75. If a participants misses study assessment visits, they will still be invited to conduct a study close-out visit at six months and complete the end of study survey.

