**Primary Effectiveness Outcomes (compared between intervention and control groups)**				
Care Linkage	% of participants attending an outpatient visit within 14 days of discharge	EHR/admin	LR	Once/patient
Treatment Retention	% of patients with evidence of SUD treatment engagement (e.g., active prescription, visit with associated SUD diagnosis within past month)	EHR/admin	LR	At 2, 4, and 6 months

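### For the two patient-reported secondary outcomes, complete-case analysis is primary and imputation waits on an undefined amount of missing data; a model using all visits would be safer at little cost

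*Protocol article*

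**What the plan says.** The Statistical analysis section of the protocol article states: "Complete case analysis will be used as a primary approach to missing data". The next sentence reads: "If there is a large amount of missing data, multiple imputations will be used to mitigate the effects of missing data". Neither sentence separates one outcome from another, and no amount is attached to the trigger.

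Table 2 takes care linkage, treatment retention and time to first visit from EHR or administrative data. Substance use and acute care utilization are listed with the patient as source, at 2, 4 and 6 months. The text under Table 2 says that outcomes combine administrative review and Timeline Followback self-report, without saying which outcome uses which.

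Table 1 schedules Timeline Followback at follow-up visits only; the baseline substance-use instrument is TAPS. Procedures and assessments foresees missed visits and says of those participants that "they will still be invited to conduct a study close-out visit at six months".

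On size and purpose: "A total of 75 patients will be recruited"; "Randomization is unbalanced, with a ratio of 3:2 favoring the intervention arm over Usual Care"; "this trial is not designed for statistical power to definitively test effectiveness hypotheses". The regressions are run "in order to test the feasibility of our assessment and analytic strategies".

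**The concern.** Complete-case regression gives an unbiased arm comparison only if, given what is in the model, being observed is unrelated to the outcome. Three features of the design put that in doubt for the patient-reported outcomes.

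- The Intervention section gives structured post-discharge outreach to the IntACT arm only, with repeated attempts over the first three weeks for people not reached. Participants are unmasked. Attendance at study visits could therefore differ by arm.
- People who are using heavily may be the ones who miss visits.
- There is no baseline Timeline Followback value. The only same-scale predictor of a missing month-4 or month-6 value is an earlier follow-up visit, and a complete-case analysis of the later visit does not use it.

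The conditional sentence on imputation adds a second weakness. As written, whether imputation is used is settled only once the extent of missing data is known. At stake is a distorted preliminary estimate for planning the later trial, and a missing-data strategy that the pilot is meant to try out but has not fixed.

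**Working it through.** The article states no power, alpha, effect size or dropout rate, so there is no figure of its own to reproduce.

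**Inputs from the article.** 75 patients at 3:2 gives 75 × 3/5 = 45 IntACT and 75 × 2/5 = 30 Usual Care.

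**Assumed inputs.** No true effect; past-month use with SD 10 days; correlation 0.6 between an earlier and a later visit; log-odds of dropping out before the later visit rising by 1 per SD of earlier use, with the same slope in both arms; dropout (Usual Care / IntACT) of 25%/15%, 35%/20% and 45%/20%.

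**Step 1: bias.** If dropout depends only on earlier use, the later-visit mean among completers is shifted by 0.6 × (shift in earlier use among completers). The shift in earlier use comes from simulation of the assumed model.

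| Dropout UC / IntACT | Earlier-use shift, IntACT | Earlier-use shift, UC | Later shift, IntACT (×0.6) | Later shift, UC (×0.6) | IntACT minus UC |
|---|---|---|---|---|---|
| 25% / 15% | −1.32 | −2.13 | −0.79 | −1.28 | about +0.5 days |
| 35% / 20% | −1.73 | −2.93 | −1.04 | −1.76 | about +0.7 days |
| 45% / 20% | −1.73 | −3.72 | −1.04 | −2.23 | about +1.2 days |

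Usual Care loses more of its heavier users, so IntACT looks worse although nothing differs. When the later mean is estimated using the earlier visit of every participant, the difference is about 0 in all three cases.

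**Step 2: when there is no bias.** Unequal dropout alone is not enough. For a yes/no outcome with true proportion p, and follow-up probabilities r1 (good outcome) and r0 (bad outcome), the complete-case proportion is p·r1 / (p·r1 + (1−p)·r0). With follow-up of 85% in one arm and 65% in the other, unrelated to outcome, this returns p in both arms: difference 0, odds ratio 1.00. Outcome-related follow-up of 90%/70% in both arms also gives difference 0.

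**Step 3: size against random error.** In the middle case, completers are 45 × 0.80 = 36 and 30 × 0.65 = 19.5. SE = 10 × √(1/36 + 1/19.5) = 2.8 days. The bias of 0.7 is 0.7/2.8 = a quarter of one SE. With everyone observed, SE = 10 × √(1/45 + 1/30) = 2.36 days.

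**Step 4: precision that a better model can recover.** Complete-case SE relative to full data is √[(1/36 + 1/19.5)/(1/45 + 1/30)] = √1.423 = 1.19, or 19% wider. If every participant had an earlier visit and it were used fully, the variance would be 100 × [0.64 × (1/36 + 1/19.5) + 0.36 × (1/45 + 1/30)], so SE = 2.66, or 2.66/2.36 = 13% wider. Most of the widening comes from losing people and is not recoverable. Someone lost before month 2 has no earlier Timeline Followback value at all.

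**The case against.** The strongest reply is that little is exposed and the effect is small. Much of it stands.

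- **The EHR outcomes are hardly touched.** A reader might infer that complete-case analysis drops deaths and people with no follow-up record from linkage and retention. The article does not say so. Linkage is the percentage "of participants attending an outpatient visit within 14 days of discharge", and retention is the percentage with evidence of engagement. Under those definitions a participant with no visit or no evidence counts as a no. No study visit is needed for either outcome.
- **The method is not picked on the result.** A reader might infer that from the conditional imputation. The trigger is the amount missing, and Study design masks the statisticians to arm. The wording can also be read as adding imputation to a complete-case analysis that remains primary.
- **Differential follow-up is not established.** Study staff lead outcome assessment in both arms, remotely if necessary, with payment for each visit. The close-out invitation to people who missed visits is a safeguard. This makes arm differences less certain but does not remove the possibility.
- **Discarding whole participants is not stated.** A visit-by-visit regression would use everyone seen at that visit. Even so, it would not use an earlier value to inform a later missing one.
- **Pilot status and condensation.** No confirmatory effectiveness test is planned, and a numerical threshold or imputation model may sit in a fuller document, so their absence here is no finding. What remains is the stated choice of primary method. Because the comparison is meant to try out the analytic strategy, pilot status does not make that choice irrelevant.

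**Conclusion.** The point holds for the two patient-reported secondary outcomes and no further. The article fixes complete-case as primary and makes imputation conditional on an unquantified amount, in a design where missingness could plausibly differ by arm and depend on use. Bias is possible, not certain. Under the assumed inputs it is about 0.5 to 1.2 days against IntACT, against a standard error of about 2.8 days. Every dropout rate, the SD, the correlation and the dropout slope are assumptions.

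The stronger reading, that unequal dropout as such biases the trial's arm comparisons or its primary effectiveness outcomes, is not supported. Unequal dropout unrelated to outcome gives no bias, and both primary effectiveness outcomes come from records. This is a modest improvement worth making, and it does not threaten the pilot's conclusions. Acute care utilization belongs here as Table 2 sources it; to the extent that administrative data supply it, the exposure is smaller.

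**What to change.** In the Statistical analysis section, for substance use and acute care utilization:

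1. Make the primary analysis a likelihood-based repeated-measures model, in a form suited to each outcome's scale, with arm, visit, arm-by-visit and baseline TAPS, using all available visits whatever the amount missing.
2. Delete the trigger based on a large amount of missing data.
3. Keep complete-case as a sensitivity analysis.
4. Report missingness by arm and visit as a feasibility result.

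For the EHR outcomes, add one sentence confirming that all randomized participants stay in the denominator. That is a clarification, not the correction of an error.

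The cost is a few sentences and slightly more programming, with no new data. The limit should be stated too: the model removes bias only when missingness depends on observed data. It does not help if people are missing because of use that was never recorded, and it recovers little for those with no follow-up visit.

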### Safety monitoring

This single-site, minimal-risk study does not require a formal Data and Safety Monitoring Board (DSMB). Study staff will monitor participants for adverse events potentially related to the intervention or research procedures, including confidentiality breaches and emotional or mental health distress during care coordination or data collection, as well as serious clinical outcomes (e.g., ED visits, hospitalizations, overdose, death) using the EHR and patient self-report during each study visit. Events that meet IRB reporting criteria will be reported according to institutional policy, and study procedures will be modified or paused if emerging safety concerns are identified.

### Ethics and dissemination

All study activities were approved by the University of Utah Institutional Review Board (#00195935). Study activities will be carried out in accordance with the ethical standards set forth in the Declaration of Helsinki. The results of this study will be disseminated in peer reviewed manuscripts.

### Trial status

The initial protocol for the IntACT trial received IRB approval in January 2026. The study and intervention teams were finalized in March 2026. The trial protocol was registered on Cliincaltrials.gov on May 11, 2026. Recruitment is scheduled to begin on June 21, 2026. We anticipate that enrollment will be complete by July 31, 2027. Data collection will be completed by February 28, 2028. Trial results are expected by May 31, 2028. This manuscript was based on the IRB-approved protocol (version 2.0).

## Discussion

This paper describes the study design and protocol for a pilot RCT evaluating a novel primary care-based care transition intervention for hospitalized patients with SUD. The IntACT intervention holds promise to address an important gap in SUD care – connecting individuals to longitudinal SUD and medical treatment following a hospitalization. Currently there are few rigorously studied models to support patients with SUD during post-hospitalization care transitions, leading to a dearth of guidance for health systems seeking to implement SUD care transition supports tailored to their respective environments. Given the high prevalence of SUD among hospitalized patients nationwide, identifying models that are effective and adaptable to a range of healthcare settings could have major implications for future research, clinical care, and health policy.

A strength of the IntACT model is its integration within primary care. Primary care-based interventions have a strong potential for scalability given the geographic reach of primary care nationwide. The team-based design of IntACT is also well-suited to modern primary care settings, which have increasingly prioritized the implementation of team-based care models [54,55]. Further, core features of IntACT, such as care management and remotely-delivered medical care, are already ingrained into many US primary care settings. However, integrating SUD treatment into primary care settings has proven challenging, with few primary care clinicians prescribing medications for SUD like buprenorphine [56–58]. Previous studies have identified factors such as a lack of local mentorship and support as factors that influence SUD care adoption [59–61]. Whether an integrated addiction care team co-managing new patients with SUD will help to overcome these barriers is unknown. The IntACT study includes a mixed methods assessment of IntACT’s acceptability and implementation among both hospital-based and outpatient clinicians. These measures can yield key information aimed at enhancing IntACT’s integration with primary care to inform intervention adaptation for future large-scale studies that include more diverse practice settings.

Another strength of this study is that the intervention spans care settings that are often siloed during post-hospitalization care transitions [15]. While the IntACT team is based in primary care, the intervention begins with in-reach to meet enrolled participants while they are still hospitalized. This step enables one clinical team to provide continuity of care before discharge, during the immediate post-hospitalization period, and then longitudinally for the following four months. There are numerous theoretical advantages to this approach, including providing interdisciplinary support during discharge planning, establishing rapport and exchanging accurate contact information with patients prior to discharge, and allowing for stronger lines of communication between inpatient and outpatient care settings. However, these advantages come at the cost of dedicated effort required to mobilize to the hospital and provide intensive care coordination after discharge. The IntACT study includes measures of feasibility that include cost estimates and post-discharge acute care utilization that will help to elucidate the financial sustainability of the model and which can inform future adequately-powered cost-effectiveness studies.

Finally, the team-based design of IntACT is a key feature that will be evaluated in this pilot study. Interdisciplinary teams bring complementary expertise that can confer synergy to complex clinical episodes like SUD care transitions. However, there are also additional investments required by health systems to support staff, training, and infrastructure (e.g., cell phone) for team-based care. The IntACT study includes both quantitative and qualitative assessments with intervention team members, clinicians who interact with the intervention, and patient participants to learn about the feasibility, unique benefits, and required investments for a team-based care transition intervention. The cost analysis will add another element of assessment to generate hypotheses about the relative benefits and costs of team-based models that can be studied in future comparative effectiveness studies with other types of interventions such as individual (e.g., a single care manager) models. The study’s use of established implementation science frameworks like PRISM and RE-AIM provide tools to contextualize our findings and inform conclusions about the implementation of team-based care to support SUD care transitions in general medical settings.

### Limitations

There are several limitations with this pilot study. By design, the study is conducted at a single-site involving a sample that lacks statistical power to generate definitive conclusions about effectiveness. Rather, this study is designed to assess the feasibility of intervention implementation and study design to inform future research. A second limitation is that the study relies predominantly on subjective assessment instruments such as patient recall, survey responses, and interviews, which are prone to social desirability bias and other potential confounders. However, the study predominantly uses validated survey instruments for quantitative assessment, and complementary qualitative data provides analytic depth to inform preliminary conclusions about the intervention. Finally, the composition of the IntACT team, which includes a Board-certified addiction specialist, a nurse care manager, and a peer support specialist, may not be generalizable to all practice settings. The IntACT study intends to lay the groundwork for future research on team-based models that can be adapted to diverse practice settings using locally-available personnel.

## Conclusion

The IntACT study is a single-site pilot RCT that will evaluate the feasibility and preliminary effectiveness of a novel primary care-based care transition intervention for hospitalized individuals with SUD. Given the pressing need to expand access to SUD treatment in the US, identifying promising interventions that proactively identify patients with SUD in high prevalence settings and facilitate linkage to longitudinal, comprehensive healthcare and SUD treatment is a crucial objective. The results of this pilot study can inform future broad implementation and evaluation of interventions designed to enhance care for hospitalized individuals with SUD.

